## Abstract

**Background:**

Motivational interviewing (MI) has great potential in changing health-related behaviors. In addition to delivery in face-to-face individual counseling, MI can be delivered through online groups, a method that is particularly appealing to adolescents and may offer several benefits. This randomized controlled trial compares the effectiveness of prevailing health education (HE), face-to-face individual MI and online group MI in improving adolescents’ oral health behaviors (diet and toothbrushing) and in preventing dental caries and periodontal diseases.

**Methods/Design:**

In each of Hong Kong’s main districts (Hong Kong Island, Kowloon and the New Territories), three secondary schools will be recruited and randomly assigned to three groups (HE, face-to-face individual MI, and online group MI). A total of 495 adolescents (aged 12 to 13 years) with unfavorable oral health behaviors (“snacking twice or more a day” and/or “brushing teeth less than twice a day”) will be recruited: 165 in each group. Two dental hygienists will be trained to deliver the interventions. HE will be provided through an oral health talk. Participants in the “face-to-face individual MI” group will join a one-on-one counseling session. For “online group MI,” participants will form groups of 6 to 8 and join a synchronous text-based online counseling session. At baseline and after 6, 12 and 24 months, clinical outcomes (caries increment and gingival health) and oral health self-efficacy and behaviors (toothbrushing and snacking) will be recorded through an oral examination and a questionnaire, respectively. Effectiveness of the interventions will be evaluated and compared. The primary outcomes will be the “number of new carious surfaces” and “gingival bleeding score” (% of surfaces with gingival bleeding). The secondary outcomes will be changes in oral health self-efficacy and behaviors (toothbrushing and snacking frequencies). A preliminary economic evaluation and a process evaluation will be included to analyze the cost of the interventions and the interactions in MI sessions.

**Discussion:**

Since online group MI is expected to be more convenient, accessible, and time efficient, it might address the practicality issues and pave the way for the application of MI in dental practice. The findings will assist public health workers and dental practitioners to choose effective and viable approaches in delivering behavioral interventions. Since unhealthy diet and poor personal hygiene are common risk factors accountable for many systemic diseases, the intervention scheme identified in this study can also contribute to advancing general health.

**Trial registration:**

The HKU Clinical Trial Register #HKCTR-1852 (registered on 13 November 2014).

## Background

Common oral diseases such as dental caries (tooth decay) and periodontal diseases (gum diseases) are highly prevalent and afflict a large proportion of the world’s population [1]. The treatment of these diseases and their complications imposes a heavy financial burden on families and the society [2]. Like other chronic diseases, dental caries and periodontal diseases are highly determined by one’s “lifestyles” and are preventable if one can adopt healthy dental behaviors [1]. Two oral health self-care behaviors, namely brushing teeth twice a day and avoiding frequent snacking, are considered central to the protection of oral health [3].

Prevailing health education (HE) focuses on disseminating information and giving normative advice. A typical consultation is often an exercise in overt persuasion. However, what appears to be a convincing line of reasoning to the professionals may not be of interest to the clients or may even result in the clients’ resistance to change [4]. The insufficiency of HE in promoting oral health has been documented [5]. Although oral health knowledge can often be improved, such knowledge gain seldom translates into sustained changes in behaviors [5].

Addressing the insufficiency of HE, a person-centered counseling approach, motivational interviewing (MI), has been developed [6]. As a collaborative, goal-oriented style of communication, MI explores a client’s ambivalence and elicits client’s intrinsic motivation for and commitment to behavioral changes within an atmosphere of acceptance and compassion [4]. Its effectiveness in changing a broad range of behaviors, such as lack of physical exercise, unhealthy diet and poor compliance to medication, has been reported [7]. Motivational interviewing has been introduced into changing oral health related behaviors [8] and has demonstrated its potential in preventing early childhood caries [9, 10] and in treating adult patients with periodontitis [11, 12]. Nevertheless, its effectiveness in changing adolescents’ dental behaviors and protecting their oral health is yet to be investigated. Since adolescence is a critical stage when health habits are reinforced and perpetuated, interventions at this age are essential for combating oral diseases over a lifetime [3]. The latest oral health survey in Hong Kong has shown that 32 % of the adolescents did not brush teeth twice a day and that 36 % snacked twice a day or more often [13]. These data point to the need for behavioral interventions in this age group.

MI has been typically delivered through face-to-face individual (one-on-one) sessions, but this is not the only possible mode of delivery [4]. MI can also be adapted for delivery via other media (telephone, mails, Internet etc.) [4] or in a group format [14]. Online groups are considered promising vehicles for delivering MI to adolescents [15, 16]. Internet use has grown exponentially and has become an appealing channel through which young people interact with the world [17]. Meanwhile, the sensitivity of youth to their peers makes group work a powerful strategy for health intervention [14, 18]. More than just an alternative delivery mechanism, online group MI may offer several benefits that face-to-face individual MI cannot provide. For example, (a) it connects isolated individuals to a collaborative group where interactions take place between facilitator and participants, and also among participants themselves [14, 15]; (b) members can be inspired by others’ ideas and perspectives, which broaden the way they think about their lives’ possibilities and serve as a catalyst for them to move toward change [19]; (c) members often benefit from the support and experience of others in similar situations, gain hope and confidence that make their challenges more manageable, and discover their own path forward [19]; (d) online counseling offers a high level of anonymity, reduces embarrassment and stigma, and facilitates members’ openness and self-disclosure [20, 21]; (e) online sessions are convenient, allow members to access within the comfort of their own home, and have the potential to involve those hard to reach people [21]; and (f) online group MI, serving several members at once, are likely to be time-efficient and cost-effective, and may be a more practical approach [22].

Two pilot studies have been carried out to test online group MI among 20 adults with obesity [23] and 26 adolescent smokers [15]. Both studies supported the acceptance and feasibility of online group MI and provided preliminary evidence on its usefulness. Online group MI helped adult participants reduce weight by 2.6 kg on average in 8 weeks, reduced the amount adolescents smoked per day (4.4 to 2.4; *P* = 0.023), and increased their intention to quit (*P* = 0.038). Both pilot studies were uncontrolled, single-group trials with a small sample size and self-reported outcomes. To further test the effectiveness of online group MI, a randomized controlled trial was conducted among 136 adolescent smokers [16]. Adolescents who participated in the online group MI (n = 77) were significantly more likely than controls (n = 59) to report abstinence from smoking, fewer smoking days, and a reduction in the amount smoked after 3 months (all *P* < 0.05). Face-to-face individual MI was not, however, included in the comparison. While these early reports suggest the promises of online group MI, this mode of delivery has not been introduced to and tested in changing oral health behaviors.

This study aims to evaluate and compare the effectiveness of prevailing health education, face-to-face individual MI, and online group MI in enhancing adolescents’ oral health self-efficacy, improving their oral health behaviors (toothbrushing and snacking) and preventing common oral diseases (dental caries and periodontal diseases). The null hypothesis is that there is no difference in the effectiveness of the three interventions in changing adolescents’ oral health self-efficacy and behaviors and in preventing dental caries and periodontitis.

## Methods/Design

### Sample size calculation

The primary outcomes of this study are the “number of new carious surfaces” (∆DMFS) and “gingival bleeding score” (% of surfaces with gingival bleeding). An effect size of 0.4 (based on means) is considered clinically significant for both variable [24]. Based on a significance level of 5 % and a targeted statistical power of 80 %, 132 participants in each group will be required. Allowing for a 20 % attrition rate, 165 participants would need to be recruited into each of the three study groups. The total sample size will be 495.

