### Participant recruitment and randomization

CONSORT guidelines [25] will be followed in the design, implementation and reporting of this randomized controlled trial. The protocol of this study was reviewed, and ethical approval was granted by the institutional review board of the University of Hong Kong and the Hospital Authority Hong Kong West Cluster (IRB #UW14-142).

To be eligible to join this study, a participant should (a) be a Form-1 or Form-2 student (aged 12 to 13 years) in a participating school, (b) have unfavorable oral health behavior(s) (that is, be a student who needs intervention), and (c) have Internet access via computers or mobile devices (smart phone, iPad etc.). Unfavorable oral health behaviors are defined as “snacking twice or more a day” and/or “brushing teeth less than twice a day.” A student will be excluded if he/she (i) is unable to cooperate in the related procedures due to severe health conditions, (ii) cannot speak Cantonese or (iii) cannot read and type Chinese.

This study will be conducted in nine secondary schools; three in each of Hong Kong’s three main districts (Hong Kong Island, Kowloon and the New Territories). All schools are co-ed schools, both sexes are included, and there is a balance in sexes across groups. The three schools in each district will be randomly allocated by the drawing of lots in sealed envelopes to one of three groups: (1) HE, (2) face-to-face MI or (3) online group MI. The group allocation will be done by a researcher not involved in delivering the intervention and assessing the outcomes.

All Form-1 and Form-2 students in the participating schools will be approached. Parental written consent and student’s assent will be obtained on their participation. Eligible participants will be identified through a standardized questionnaire on students’ demographic information, current snacking and toothbrushing habits, access to the Internet and language proficiency. The recruitment process will be monitored to ensure the characteristics of participants across the three groups are balanced with regard to their socio-demographic profile (sex and parental education level) and baseline behaviors (snacking and brushing). In the three schools allocated to each intervention group, 165 participants will be recruited; 55 from each school. The total number of participants will be 495 for the whole study.

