## Discussion

To the best of our knowledge, this study is the first attempt to introduce other mode of MI delivery, besides face-to-face individual counseling, into dental interventions. It taps into an unexplored area and is likely to generate useful evidence. Since online group MI is expected to be more convenient, accessible, and time efficient, it might address the practicality issues and pave the way for the application of MI in dental practice. The inclusion of online interventions into this study is also in line with the trend of Telehealth, in which information and communication technology is incorporated into health care delivery and is transforming the practice in many areas [30].

In this trial, randomization will be carried out at school level, instead of at individual level. Students in each participating school will receive the same intervention. This is to avoid intervention contamination, which is likely to happen if students in the same school are assigned to different groups. By randomly assigning the three schools from each district into three different groups and by monitoring the recruitment process, a balance will be reached in the characteristics of participants in the different groups with regard to their sociodemographic background and baseline behaviors. Since MI can rarely be completed in a single contact, follow-up phone calls will be made after the counseling session to assist the start of changes, explore solutions to the problems encountered, promote maintenance, avoid relapse and help re-establish change. Follow-up phone calls will not, however, be made in the HE group, so that the intervention reflects precisely the prevailing health education practice. The outcomes of the interventions will be evaluated by using psychological, behavioral and clinical measures at three points of time. This will allow us to interpret the results in a more complete manner.

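### Whole schools are randomised, three per arm, but the sample size makes no allowance for clustering, so the stated 80 % power is not delivered

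*Protocol article*

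**What the plan says.** The section Sample size calculation names two primary outcomes, new carious surfaces and the gingival bleeding score. It sets one target for both: "An effect size of 0.4 (based on means) is considered clinically significant for both variable". With 5 % significance and 80 % power it arrives at "132 participants in each group will be required". The only later adjustment is for 20 % attrition, giving 165 per group and 495 in total.

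The section Participant recruitment and randomization describes a cluster design: "This study will be conducted in nine secondary schools; three in each of Hong Kong’s three main districts", and "The three schools in each district will be randomly allocated by the drawing of lots in sealed envelopes to one of three groups". It adds: "In the three schools allocated to each intervention group, 165 participants will be recruited; 55 from each school". The Discussion confirms that "randomization will be carried out at school level, instead of at individual level" and gives avoidance of contamination between pupils of one school as the reason.

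**The concern.** The calculation lists its inputs, and none of them reflects the randomisation of schools. Pupils of one school cannot be assumed independent. The article itself expects them to influence one another, since that is why it randomises schools. The health education talk goes to a whole school at once, and online MI runs in groups of six to eight pupils.

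Two things follow. Each pupil adds less information than an independent pupil would. And the comparison between arms rests on nine schools, so it has few degrees of freedom however many pupils are examined. If power is well below 80 %, a null result may be read as showing that MI is no better than health education, when the design could reliably detect only a much larger effect.

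**Working it through.** **Inputs from the article.** Effect size d = 0.4, read as a standardised mean difference; 5 % significance, taken as two-sided because sidedness is not stated; 80 % power; 132 evaluable per arm; 20 % attrition; 3 schools per arm; 55 pupils per school, so 55 × 0.8 = 44 evaluable (132 / 3 = 44).

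**Assumed input.** The ICC, over a range, because the article gives none.

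**Step 1: reproduce 132.** For independent pupils, n per arm = 2 × [(z for alpha + z for power) / d]².
- Stated inputs: 2 × [(1.960 + 0.842) / 0.4]² = 98.1, so 99.
- 90 % power instead of 80 %: 131.3, so 132.
- 80 % power with 5 % split over three pairwise comparisons: 130.9, so 131 (133 by the t test).

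The stated inputs therefore do not give 132. Two unstated variants do, or nearly so, and both are formulas for independent individuals. The attrition step is correct: 132 / 0.8 = 165, and 3 × 165 = 495.

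**Step 2: apply the design.** Design effect DE = 1 + (44 − 1) × ICC. Effective n = 132 / DE. Standard error of a difference between two arms, in SD units, = √(2 × DE / 132). Power comes from the noncentral t distribution with noncentrality 0.4 / SE. Degrees of freedom are 9 − 3 = 6 with the variance pooled over three arms, or 9 − 1 − 2 − 2 = 4 once districts are fitted as blocks. The 5 % critical values are 2.447 and 2.776.

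| ICC (assumed) | DE | Effective n per arm | SE | 0.4 / SE | Power, 6 df | Power, 4 df | Effect with 80 % power, 6 df |
|---|---|---|---|---|---|---|---|
| 0 | 1.00 | 132 | 0.123 | 3.25 | 77 % | 69 % | 0.41 SD |
| 0.01 | 1.43 | 92 | 0.147 | 2.72 | 62 % | 54 % | 0.50 SD |
| 0.02 | 1.86 | 71 | 0.168 | 2.38 | 52 % | 44 % | 0.57 SD |
| 0.05 | 3.15 | 42 | 0.218 | 1.83 | 34 % | 29 % | 0.74 SD |

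Simulated t tests on school means gave 62 %, 51 % and 33 % at ICCs of 0.01, 0.02 and 0.05, in agreement with the 6-df column.

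**Step 3: can more pupils per school help?** As schools grow, effective n per arm approaches 3 / ICC. Setting 3 / ICC = 98.1 gives an ICC of 0.031. Above that value, three schools per arm cannot reach 80 % power for 0.4 SD at any school size, even by the normal approximation.

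**The case against.** **132 is a third larger than the 99 that the stated inputs give, so some allowance may be built in.** The surplus is real and unexplained. The text does not attribute it to clustering, and it equals what 90 % power gives for independent pupils. Taken as a clustering allowance, it covers a design effect of 132 / 98.1 = 1.35, an ICC of 0.35 / 43 = 0.008, and only if the few degrees of freedom are ignored. The table already uses all 132 pupils at an unadjusted 5 %, so the surplus is credited. If it came from a three-way split of alpha, power is lower still: 38 % on 6 df at ICC 0.01.

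**The planned analysis may not use a test on 4 to 6 degrees of freedom.** The Statistical analysis section plans ordinary comparisons of means, with school as one factor among several in ANCOVA and regression. A pupil-level test that ignores clustering would reject at 0.4 SD in about 86 %, 83 % and 77 % of trials at ICCs of 0.01, 0.02 and 0.05. But its type I error would be about 10 %, 15 % and 27 % instead of 5 %, so those rates are not usable power. This adds a risk of false positives. A fixed school factor does not help, because each school lies wholly within one arm.

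**The ICC is assumed, and blocking and covariates could recover power.** This limits the precision of the figures. As an illustration, if covariates explained 25 % of the variance at both levels, power on 6 df would be about 81 % at ICC 0.005, but 74 %, 63 % and 43 % at 0.01, 0.02 and 0.05. The target could be met at a very small ICC with useful covariates. The article claims neither, and over the range from 0.01 upward the shortfall remains.

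**The full protocol may state an ICC.** The article sets out its calculation with inputs and result, so the point concerns a stated claim and not an omitted detail.

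**Conclusion.** The concern holds. The 80 % claim is not supported for the design described. For 0.4 SD, power is about 62 % to 34 % on 6 degrees of freedom and 54 % to 29 % on 4, for ICCs from 0.01 to 0.05. Without covariate adjustment, a test based on between-school variation misses 80 % even at an ICC of zero.

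The exact shortfall depends on the assumed ICC, on equal schools of 44 evaluable pupils, on a two-sided unadjusted 5 % level, and on no gain from covariates or from variance removed by districts. That the calculation contains no clustering allowance does not depend on these. The point applies to both primary outcomes and must be corrected.

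**What to change.** Keep the nine schools and 495 pupils, and rewrite the power paragraph in Sample size calculation:

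- State that the trial is cluster randomised, with 3 schools of about 44 analysed pupils per arm.
- Remove the unqualified 80 % claim. Give power and detectable effect over a stated ICC range, with the between-school degrees of freedom. For ICCs from 0.01 to 0.05 on 6 df this is about 62 % to 34 % power for 0.4 SD, or 80 % power for 0.50 to 0.74 SD. Label the ICCs as assumptions, or give their source.
- Explain how 132 was obtained, including any split of alpha.
- Say that a non-significant result will be interpreted from its confidence interval.

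The Statistical analysis section should match, with school as the unit of analysis or as a random effect with a small-sample correction. Otherwise the new statement would describe a test that is not planned.

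The cost is one reworded paragraph, a matching line in the analysis section and a less favourable power figure. No participants are added. If 80 % power for 0.4 SD is to be kept, the remedy is more schools, not more pupils per school: at 44 evaluable pupils each, with 2 × (schools per arm − 1) degrees of freedom, about 5, 6 or 9 schools per arm at ICCs of 0.01, 0.02 and 0.05. The Trial status section says schools were still being contacted, so that option can be weighed.

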### Participant recruitment and randomization

CONSORT guidelines [25] will be followed in the design, implementation and reporting of this randomized controlled trial. The protocol of this study was reviewed, and ethical approval was granted by the institutional review board of the University of Hong Kong and the Hospital Authority Hong Kong West Cluster (IRB #UW14-142).

To be eligible to join this study, a participant should (a) be a Form-1 or Form-2 student (aged 12 to 13 years) in a participating school, (b) have unfavorable oral health behavior(s) (that is, be a student who needs intervention), and (c) have Internet access via computers or mobile devices (smart phone, iPad etc.). Unfavorable oral health behaviors are defined as “snacking twice or more a day” and/or “brushing teeth less than twice a day.” A student will be excluded if he/she (i) is unable to cooperate in the related procedures due to severe health conditions, (ii) cannot speak Cantonese or (iii) cannot read and type Chinese.

This study will be conducted in nine secondary schools; three in each of Hong Kong’s three main districts (Hong Kong Island, Kowloon and the New Territories). All schools are co-ed schools, both sexes are included, and there is a balance in sexes across groups. The three schools in each district will be randomly allocated by the drawing of lots in sealed envelopes to one of three groups: (1) HE, (2) face-to-face MI or (3) online group MI. The group allocation will be done by a researcher not involved in delivering the intervention and assessing the outcomes.

All Form-1 and Form-2 students in the participating schools will be approached. Parental written consent and student’s assent will be obtained on their participation. Eligible participants will be identified through a standardized questionnaire on students’ demographic information, current snacking and toothbrushing habits, access to the Internet and language proficiency. The recruitment process will be monitored to ensure the characteristics of participants across the three groups are balanced with regard to their socio-demographic profile (sex and parental education level) and baseline behaviors (snacking and brushing). In the three schools allocated to each intervention group, 165 participants will be recruited; 55 from each school. The total number of participants will be 495 for the whole study.

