For online group MI, participants who share the same unfavorable behavior(s) (that is, infrequent toothbrushing, snacking, or both) will form a group of six to eight [14] and join an online MI session led by a dental hygienist. Through an online chat room created in a secure server, the synchronous (real time) text-based online session lasts for 30 to 45 minutes and follows the MI principles and group facilitation strategies. The session starts with a simple welcome and orientation, so that members become acclimated to the group setting and have an agreement on the topics of focus for the group. During the *engagement* phase, the counselor helps members become comfortable with participating and focuses on facilitating early group process on members’ issues and concerns. As the group moves into the *exploring perspectives* phase, the counselor helps deepen members’ interactions as they explore their individual viewpoints and situations together. During the *broadening perspectives* phase, interactions continue to deepen and broaden as the counselor encourages members to consider new possibilities, to allow buried hopes to reemerge and to take others’ perspectives into consideration. During the *moving into action* phase, the counselor guides members to develop specific change plans, to delineate steps toward their goals, to identify high risk situations (for example, outings and social functions) and environmental factors (for example, the temptation of fast food and unhealthy cooking in their families), and to explore possible solutions transferable to their daily lives. To close the session, the counselor summarizes the perspectives gained (or abandoned) and the experiences shared, highlights any messages for members to take with them and links the themes back to the large process of change that members are undertaking. During the whole session, the counselor engages members as a group rather than as a collection of individuals. While maintaining an individualized, client-centered focus, the counselor remains attuned to group dynamics and builds group cohesion and momentum by linking members’ interest, perspectives, experiences and concerns. The counselor allows the group to unfold at a comfortable and unpressured pace and finds a balance between providing structure and allowing spontaneity.

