### Outcome measures

The primary outcomes will be the “number of new carious surfaces” (∆DMFS) and “gingival bleeding score” (% of surfaces with gingival bleeding), whereas secondary outcomes will be changes in oral health self-efficacy and behaviors (Table 2).

**Table 2 Tab2:** Outcome measures

Outcomes	Variables	Codes	Source of information
Secondary outcomes			
Change in self-efficacy^a^			
Snacking	Views on the statements “I can control snacks to once a day or less when … (under several scenarios)”	(1) Not at all; (2) A little of the time;	Questionnaire
		(3) Sometimes; (4) Most of the time;	
		(5) All the time	
Toothbrushing	Views on the statements “I can brush my teeth twice a day when … (under several scenarios)”	1) Not at all; (2) A little of the time;	Questionnaire
		(3) Sometimes; (4) Most of the time;	
		(5) All the time	
Change in behaviors			
Snacking	Frequency of snacking per day	(1) None; (2) Once; (3) Twice;	Questionnaire
		(4) 3 times; (5) 4 times or more	
Toothbrushing	Frequency of toothbrushing per day	(1) Less than once; (2) Once;	Questionnaire
		(3) Twice; (4) 3 times or more	
Primary outcomes			
Gingival health	Gingival bleeding score (% of tooth surfaces with gingival bleeding)	Continuous	Oral examination
Caries increment	Number of new carious surfaces	Continuous	Oral examination
	Presence/absence of new carious surfaces	Nominal	Oral examination

^a^Six scenarios will be used, namely “when feeling down in the dumps,” “when busy and overloaded,” “when tired,” “when on a vacation,” “when it means stopping doing something that is enjoyable” and “if there is a slip up, will the subject resume controlling”

At baseline and after 6, 12 and 24 months, participants will be examined by a trained dentist calibrated against an experienced oral epidemiologist. The examiner will be blinded to the group allocation of each school. Dental caries will be registered by following the International Caries Detection and Assessment System (ICDAS), which differentiates seven stages of caries development (from sound to early enamel lesion to extensive cavity) [27]. Gingival health will be evaluated using the Gingival Bleeding Index [28]. Participants will be examined in a supine position, with an illuminated mouth mirror and a CPI probe. The tooth status will be assessed by visual inspection, aided by tactile inspection if necessary. Duplicate examinations will be carried out on 10 % of the participants to assess intraexaminer reliability.

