Before each oral examination, a questionnaire will be completed by the participants on a self-administered basis to gather information on their sociodemographic background and oral health knowledge, self-efficacy and behaviors. For oral health behaviors, participants will be asked how many times they snack and brush their teeth in a day. Their oral health self-efficacy will be measured by asking the participants whether they can “control snacks to once a day or less” and “brush teeth at least twice a day” under six scenarios, namely “when feeling down in the dumps,” “when busy and overloaded,” “when tired,” “when on a vacation,” “when it means stopping doing something that is enjoyable,” and “if there is a slip up, will the subject resume controlling” [29]. Participants are required to rate their control of oral health behaviors among “not at all,” “a little of the time,” “sometimes,” “most of the time” and “all the time.”

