### Statistical analysis

Data will be analyzed using the computer software Statistical Package for Social Sciences (SPSS). Effectiveness of the intervention schemes over 6, 12 and 24 months will be evaluated on an intention-to-treat basis. All participants randomly assigned to each group will be included in the analysis, regardless of whether they receive the intervention or complete the study. If a participant is lost to follow-up, the last known outcome status will be carried forward.

Chi-square tests will be used for comparing distributions, whereas parametric or nonparametric methods, as appropriate, will be adopted for comparing means. Effect sizes (relative risk) and their 95 % confidence intervals (95 % CI) will be calculated and reported with *P* values. Multivariate analysis, namely ANCOVA (analysis of covariance) and multiple regressions, will be performed to evaluate the effects of various factors (intervention, school, counselor, participant’s sex, socioeconomic background and baseline caries experience) on the outcomes.

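### Pupils qualify on either of two habits, but change in both is compared in everyone and the stated models omit baseline behaviour

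*Protocol article*

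**What the plan says.** Under Participant recruitment and randomization, one habit is enough for entry: "Unfavorable oral health behaviors are defined as “snacking twice or more a day” and/or “brushing teeth less than twice a day". A frequent snacker who already brushes twice a day is eligible, and so is the reverse.

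Under Outcome measures, "secondary outcomes will be changes in oral health self-efficacy and behaviors". Table 2 lists snacking and toothbrushing separately, each with a frequency item and a self-efficacy item. Both habits are recorded in every pupil: "participants will be asked how many times they snack and brush their teeth in a day".

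Under Statistical analysis, the analysis set is everyone: "All participants randomly assigned to each group will be included in the analysis, regardless of whether they receive the intervention or complete the study". The factors named for ANCOVA and regression are intervention, school, counselor, sex, socioeconomic background and baseline caries experience. Baseline brushing, baseline snacking and the qualifying habit are not among them.

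The article uses the distinction elsewhere. In the online arm, "participants who share the same unfavorable behavior(s) (that is, infrequent toothbrushing, snacking, or both) will form a group of six to eight". Recruitment is also to be monitored so that the arms are balanced on baseline snacking and brushing, and the Discussion repeats this intention in general terms.

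**The concern.** Improving brushing and snacking is part of the stated aim and of the null hypothesis. A pupil already at target on one habit has little or no intended change to make on it. Each behavioural comparison therefore averages the effect in pupils who had the habit with a probably smaller effect in pupils who did not, and the reported size depends on the mix of the two.

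The mix can also differ between arms by chance. Allocation is by school, with three schools of 55 pupils per arm, so one school with an unusual mix carries a third of its arm. The covariate list is written out and has a baseline term for caries, but none for the behaviours that are themselves outcomes.

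**Working it through.** **Sample size.** 132 / (1 − 0.20) = 165 per arm, as stated. The 132 rests on an effect of 0.4 SD for the two clinical outcomes. It is reproduced at 80 % power with a two-sided alpha of 0.05/3 (131 by the normal approximation, 132.3 by the t-test), an adjustment that the text does not state. No behavioural outcome enters it, so this point leaves it unchanged.

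**Share already at target.** The inputs are the Background survey figures: "32 % of the adolescents did not brush teeth twice a day and that 36 % snacked twice a day or more often". The overlap of the two habits is not given, so it is varied.

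- P(either) = 0.32 + 0.36 − P(both)
- share at target on brushing = 1 − 0.32 / P(either)
- share at target on snacking = 1 − 0.36 / P(either)

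| Overlap assumed | P(both) | P(either) | At target, brushing (of 165) | At target, snacking (of 165) |
|---|---|---|---|---|
| Complete | 32 % | 36 % | 11.1 % (18) | 0 % (0) |
| Some clustering (illustration) | 20 % | 48 % | 33.3 % (55) | 25.0 % (41) |
| Independence | 11.5 % | 56.5 % | 43.3 % (72) | 36.3 % (60) |
| None | 0 % | 68 % | 52.9 % (87) | 47.1 % (78) |

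Under independence: P(either) = 1 − 0.68 × 0.64 = 0.565; brushing 1 − 0.32/0.565 = 0.433; snacking 1 − 0.36/0.565 = 0.363.

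**Dilution of a mean change.** Average effect = p × (effect in pupils with the habit) + (1 − p) × (effect in pupils at target), where p is the share with the habit. If the second effect is zero, the average is p times the first. Under independence p is 0.567 for brushing and 0.637 for snacking; across the bounds it is 0.47–0.89 and 0.53–1.00. Zero is the worst case.

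**Imbalance.** Suppose a fraction q of pupils with the habit improve whatever their arm, and none of those at target do. If the share with the habit differs between arms by δ, a difference of q × δ appears with no treatment effect. With q = 30 %, an assumed value, each percentage point of imbalance produces 0.3 points.

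**Relative risk and precision.** Assume that 30 % versus 50 % of pupils with infrequent brushing improve, and that habits are independent.

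- Among those pupils: RR = 0.50 / 0.30 = 1.67.
- All pupils, outcome is being at target, nobody relapses: (0.433 + 0.567 × 0.5) / (0.433 + 0.567 × 0.3) = 0.717 / 0.603 = 1.19.
- All pupils, outcome is improvement: (0.567 × 0.5) / (0.567 × 0.3) = 1.67, no attenuation.
- Test statistic for improvement, ignoring clustering: 93 per arm, 30 % v 50 %, z = 0.20 / √(2 × 0.40 × 0.60 / 93) = 2.78. All 165 per arm, 17.0 % v 28.3 %, z = 0.113 / √(2 × 0.227 × 0.773 / 165) = 2.46. The ratio is about 1.13. An equal-SD calculation would give 1/√0.567 = 1.33, but if pupils at target barely change, the SD in the full set is smaller.

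**The case against.** Analysing all randomised pupils answers a legitimate question: what the programme does in the population it enrols. Dilution is not bias. Pupils at target can still move, because the frequency scales have a category beyond the target and several short of it. Over 24 months, preventing relapse is a real benefit that a restricted analysis would miss. Brushing twice a day does not imply top self-efficacy when tired or on holiday. Only the online arm is described as grouped by habit: the health education talk covers both habits, and the face-to-face session follows the change the pupil chooses. Balance on baseline behaviours is monitored, the outcomes are changes from baseline, and a statistical analysis plan that is not shown may add covariates.

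Most of this stands. It rules out making the restricted set the main analysis, and it makes zero effect in pupils at target a limiting case. It does not remove the point about the models. Monitoring does not guarantee balance with three schools per arm. Taking a change score does not adjust for baseline, because pupils at and off target have different room to move. The article itself spells out the covariates and leaves these out.

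**Conclusion.** The point holds for the secondary behavioural and self-efficacy outcomes only. As written, each comparison mixes pupils with and without the habit in question, and the stated models do not account for which is which. The share at target is 11–53 % for brushing and 0–47 % for snacking, and 43 % and 36 % if the habits are independent. All of these assume that the survey rates apply to the recruited schools.

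A reader might infer more, and the documents do not support it:

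- That about two-fifths of pupils are at target is not a fact of the plan. It needs independence; with the illustrative 20 % joint prevalence the shares are 33 % and 25 %.
- That relative risks are pulled toward 1 (1.67 to 1.19) needs an outcome of being at target at follow-up. Table 2 lists change in behaviours, and the event for the relative risk is not defined. With improvement as the event, the ratio stays at 1.67.
- That restriction raises signal-to-noise by a third rests on an equal-SD assumption at odds with its own premise; on the same illustrative inputs the gain is about 1.13.
- No power loss can be stated, because the article gives no effect size for the behaviours.

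**What to change.** In Statistical analysis, for the models of brushing, snacking and self-efficacy, add as covariates the baseline value of the outcome modelled and the qualifying pattern (brushing only, snacking only, both). Enter baseline frequency as a score: entered as a full set of categories, it already determines whether the pupil is at target on that habit and so overlaps with the pattern. Keep all randomised pupils as the main analysis. Prespecify a supportive analysis of each behaviour in pupils who had that unfavourable behaviour at baseline, and report the observed mix by arm and school.

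The covariates give precision and protection against imbalance. They do not undo the dilution, which is why the supportive analysis is needed. That subset is defined by a variable measured at baseline, so pupils can still be analysed as allocated within it. The cost is wording only, since the baseline questionnaire already collects the data. The supportive analysis has fewer pupils (under independence about 93 of 165 per arm for brushing and 105 for snacking) and does not show relapse or movement beyond the target in the others.
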